## Abstract

**Background:**

Mesenchymal stromal cells (MSC) may serve as an attractive therapy in renal transplantation due to their immunosuppressive and reparative properties. While most studies have used autologous MSCs, allogeneic MSCs offer the advantage of immediate availability for clinical use. This is of major importance for indications where instant treatment is needed, for example allograft rejection or calcineurin inhibitor toxicity. Clinical studies using allogeneic MSCs are limited in number. Although these studies showed no adverse reactions, allogeneic MSCs could possibly elicit an anti-donor immune response, which may increase the incidence of rejection and impact the allograft survival in the long term. These safety issues should be addressed before further studies are planned with allogeneic MSCs in the solid organ transplant setting.

**Methods/design:**

10 renal allograft recipients, 18–75 years old, will be included in this clinical phase Ib, open label, single center study. Patients will receive two doses of 1.5 × 10^6^ per/kg body weight allogeneic bone marrow derived MSCs intravenously, at 25 and 26 weeks after transplantation, when immune suppression levels are reduced. The primary end point of this study is safety by assessing biopsy proven acute rejection (BPAR)/graft loss after MSC treatment. Secondary end points, all measured before and after MSC infusions, include: comparison of fibrosis in renal biopsy by quantitative Sirius Red scoring; de novo HLA antibody development and extensive immune monitoring; renal function measured by cGFR and iohexol clearance; CMV and BK infection and other opportunistic infections.

**Discussion:**

This study will provide information on the safety of allogeneic MSC infusion and its effect on the incidence of BPAR/graft loss.

Trial registration: NCT02387151

## Background

Overall kidney graft survival has improved over the past decades, mainly as a result of improvement of first-year graft survival due to better immunosuppressive regimens and overall medical care. However, long-term graft survival remained unaltered over the past two decades mainly because of graft loss due to interstitial fibrosis and tubular atrophy (IF/TA) [1]. The mechanism of IF/TA is thought to be a result of immunologic and non-immunologic causes including calcineurin inhibitor toxicity. More recently, there has been a focus on antibody-mediated rejection indicating an important role for humoral immunity in late kidney allograft failure [2–8].

In order to improve long term graft survival and minimize side effects of the current immune suppressive agents, new therapies are sought. Mesenchymal stromal cell (MSC) therapy constitutes an attractive intervention due to their immunosuppressive and reparative properties and their likely limited side effects [9]. In vitro studies imply that MSCs may play a role in modulation of immune responses. These beneficial immune modulatory effects have been confirmed in experimental models of allo- and autoimmune disorders, including allograft rejection [10–14]. First results of autologous bone marrow (BM) derived MSC therapy after human renal transplantation demonstrate safety and feasibility and illustrate their immune suppressive properties [15–22].

Most studies have used autologous MSCs. However, due to the expansion period, quality controls and logistics, product manufacturing takes several weeks, which is a long period of time for patients in need for acute treatment, for example in calcineurin toxicity and allograft rejection. Allogeneic MSCs offer the advantage of immediate availability “off-the-shelf” for clinical use. Another benefit of using allogeneic MSCs is that the cells can be selectively derived from young donors. This is important because MSC number and functionality has been shown to decrease with age [23–25]. Importantly, a potential disadvantage of allogeneic MSC treatment could be the development of an anti-donor immune response, as has been described in experimental studies [26, 27]. Therefore, it is necessary that we establish whether allogeneic MSC therapy in renal recipients is safe and does not evoke an anti-donor response, which might negatively impact graft function and survival. In the current protocol, allogeneic MSCs are infused at a time point where immune suppression levels are reduced and the graft is at increased risk for developing immune mediated injury. Additionally, a significant proportion of the grafts already has developed signs of fibrosis at this time, a process that might be reduced by the MSCs. Primary endpoints of this study include allograft rejection and graft loss. To minimize the chance of development of anti-donor immune responses and thus allograft rejection our strategy is to select allogeneic MSCs, which have no similarity with the HLA mismatches between the kidney graft and the recipient. A second criteria is that the recipient should have no preformed HLA antibodies directed to the MSCs in order to prevent immune destruction of the MSCs.

## Methods and design

### Objectives and endpoints

The primary endpoint of the current study is safety by assessing biopsy proven acute rejection (BPAR) and graft loss after allogeneic BM derived MSC treatment. The following secondary endpoints will be measured before and after MSC treatment: the level of fibrosis, as determined by quantitative Sirius Red (SR) scoring of renal biopsies; glomerular filtration rate (GFR) calculated by CKD-EPI formula and measured by iohexol clearance; Cytomegalovirus (CMV), BK infection (viremia, disease, syndrome and subtypes of BK viremia) and other opportunistic infections; the presence of anti-human leucocyte antigen (HLA) donor specific antibodies (DSA) and other phenotypical and functional aspects of the donor specific immune response.

### Study design

The current trial is a 12-month, non-randomized, open-label, prospective, single-center study. In total, 10 de novo renal recipients, 18–75 years of age, will be recruited from the transplant clinic of the Leiden University Medical Center (LUMC) and enrolled into the study if they meet the eligibility criteria. Ethical approval was obtained from the Dutch Central Committee on Research Involving Human Subjects (CCMO) and the Dutch competent authority.

### Inclusion criteria

Female or male, aged between 18 and 75 years.Subject is willing to participate in the study, must be able to give informed consent and the consent must be obtained prior to any study procedure.Recipients of a first kidney graft from a living-unrelated or non-HLA identical living related donor.Panel Reactive Antibodies (PRA) ≤50 %.Patients must be able to adhere to the study visit schedule and protocol requirements.If female and of child-bearing age, subject must be non-pregnant, non-breastfeeding, and use adequate contraception.

### Exclusion criteria

Double organ transplant recipients.BPAR in the 4 weeks before MSC infusion.Patients with evidence of active infection or abscesses (with the exception of an uncomplicated urinary tract infection) before MSC infusion.Patients suffering from hepatic failure.Patients suffering from an active autoimmune disease.A psychiatric, addictive or any disorder that compromises ability to give truly informed consent for participation in this study.Use of any investigational drug after transplantation.Documented HIV infection, active hepatitis B, hepatitis C or tuberculosis according to current transplantation inclusion criteria.Subjects with an active opportunistic infection at the time of MSC infusion [e.g., herpes zoster (shingles), CMV, BK, Pneumocystis jirovecii (PJP), aspergillosis, histoplasmosis or mycobacteria other than tuberculosis].Malignancy (including lymphoproliferative disease) within the past 2–5 years (except for squamous or basal cell carcinoma of the skin that has been treated with no evidence of recurrence) according to current transplantation inclusion criteria.Known recent substance abuse (drug or alcohol).Patients who are recipients of ABO incompatible transplants.Patients with severe total hypercholesterolemia (>7.5 mmol/L) or total hypertriglyceridemia (>5.6 mmol/L) (patients on lipid lowering treatment with controlled hyperlipidemia are acceptable).

All patients will receive alemtuzumab induction therapy at day 0 and day 1 (15 mg subcutaneously) and maintenance triple therapy consisting of prednisone, tacrolimus (Advagraf), and everolimus (Certican). The target of the everolimus is 3–8 ng/mL. The tacrolimus target is 8–10 ng/mL the first 6 weeks after transplantation, 4–7 ng/mL from week 6 to week 24 and will be reduced to targets of 1.5–3 ng/mL after week 24. Patients will receive two doses of a target of 1.5 × 10^6^ selected allogeneic MSCs per/kg body weight at weeks 25 and 26 after transplantation.

### Isolation of bone marrow and MSC production

MSCs for the study will be obtained from an independent third party donor according to the LUMC standardized and approved protocol. All donors will undergo routine examination and screening tests, according to the standard procedures required for BM donors in the LUMC. BM will be aspirated from the posterior iliac crest. A total volume of 100 to 120 mL will be harvested. The processing and expansion of the cells will take place at the Good Manufacturing Practice (GMP) Facility of the LUMC. During the expansion process, population doubling time and cell numbers are monitored as a marker for population fitness and functionality. After approval of in process and final product quality control results, the MSC products will be released for the clinical trial under a EU GMP manufacturers license. Final product release is based on the following criteria: surface marker expression (>90 % of cells CD73^+^/CD90^+^/CD105^+^, ≤1 % of cells CD45^+^ and ≤0.01 % of cells CD3^+^), absence of microbial contamination using culture and mycoplasma PCR, spindle shaped morphology, a colorless cell suspension devoid of cell aggregates, no genetic abnormalities using karyotype analysis and viability.

### Data collection

Patients enrolled in this study will undergo standard pre-transplant work-up, which consists of baseline clinical data (demographics, medical history, current medication, previous blood transfusions, percentage of PRA, infection status, physical examination, laboratory examinations, urinalysis, electrocardiogram and chest X-ray). For women, the menopausal status will be recorded and a pregnancy test will be done prior to transplantation if applicable.

Intraoperative data (warm and cold ischemia time, anatomy of donor and recipient) and background information of the kidney donor (age, gender, race, height, weight, type of allograft (living related or unrelated), infection status, serum creatinine) and HLA (mis)match will also be documented. All immunosuppressive and other drugs used and dosages administered will be recorded during the study.

### Assessment schedule

Subjects will be seen in accordance with the assessment schedule listed in Table 1.

**Table 1 Tab1:** Assessment schedule

Week	BL	Tx	W24	W25	W26	W27	W28	W30	W34	W38	W42	W46	W52
Informed consent	X												
Medical history	X	X											
Transplantation information		X											
Concomitant medication	X	X	X	X	X	X	X	X	X	X	X	X	X
Physical examination	X	X	X	X	X	X	X	X	X	X	X	X	X
Routine lab	X	X	X	X	X	X	X	X	X	X	X	X	X
Urinalysis	X	X	X	X	X	X	X	X	X	X	X	X	X
CMV, EBV and BK viral load			X	X		X		X		X		X	X
MSC infusion				X	X								
Renal biopsy		X	X										X
Iohexol clearance			X										X
Immune monitoring		X	X	X^a^	X^a^	X			X				X
DSA	X	X	X					X					X
Safety assesment	X	X	X	X	X	X	X	X	X	X	X	X	X

*BL* baseline, *Tx* renal transplantation

^a^before and 4 h after MSC infusion

### Infusion of MSCs

A clinical re-evaluation will be performed before the planned MSC infusion to rule out any contra-indication for administration. A target number of 1,5x10^6^ MSCs per/kg body weight (range 1–2 × 10^6^) will be infused IV within 30 min. Close monitoring of vital signs (temperature, pulse, respiratory rate, blood pressure and oxygen saturation) will be measured before, during and up to 2 h after MSC infusion.

### (Opportunistic) infections

Hepatitis B, C and HIV status will be evaluated routinely within 6 months before transplantation.

CMV (PCR-positive), EBV (PCR-positive), BK-viruria in urine samples and BK-viremia in blood samples (RT-PCR) will be measured as shown in Table 1. In addition subtypes of BK will be determined. Other infections (including urinary tract infections, pulmonary infections, herpes simplex) will be recorded as well. Patients are treated routinely with valganciclovir prophylaxis for 6 months except in case of a CMV negative donor and recipient status. In addition, all patients receive 6 months of cotrimoxazole prophylaxis against PJP.

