### Renal function

GFR calculation will be used to determine the renal function [28]. The following abbreviated CKD-EPI formula will be used for GFR estimation: eGFR [mL/min/1.73m2] = 141 × min (SCr/k,1)^α^ × max(SCr/k,1)^−1.209^ × 0.993^age^ × (1.018 if female) × (1.159 if black) (k is 0.7 for females and 0.9 for males, α is −0.329 for females and −0.411 for males). In addition we will measure renal function with iohexol clearance at week 24 and week 52 after transplantation [29].

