To minimize the risk of an anti-donor immune response in our study, we have chosen in our protocol to use selected allogeneic MSCs based on the before mentioned HLA criteria. In addition, patients will receive alemtuzumab induction, which according to several studies might reduce the incidence of BPAR. As maintenance therapy a combination with everolimus is used. In a heart transplant model MSC monotherapy inhibited acute graft rejection and the combination of MSCs with rapamycin induced donor-specific allograft tolerance. In the tolerant recipients, MSCs migrated to the transplanted heart and various lymphoid organs. In addition a high frequency of Tol-DCs and CD4^+^CD25^+^Foxp3^+^ T cells was found in these animals [49].

Besides extensive immune monitoring, an important secondary endpoint of our study is renal function before and after MSC treatment. In the study by Perico, renal function declined when the MSCs were administered 7 days after transplantation [16]. The hypothesis was that the subclinical inflammatory environment of the graft post transplantation favoured recruitment and activation of the MSCs, and thereby promoting a pro-inflammatory milieu with eventual acute renal dysfunction. Because the renal dysfunction could depend on the timing of infusion, in their next study MSCs were administered the day before kidney transplantation and in these patients no deterioration of renal function was seen [50]. Renal dysfunction was also not observed in our former study on a patient cohort that was treated more than 6 weeks after transplantation [17].

In addition, fibrosis in the allograft will be measured before and after MSC treatment since this is a hallmark of patients who develop allograft dysfunction [51]. It would be of interest to test whether allogeneic MSCs influence this process and could serve as therapy for IF/TA. Moreover, CMV, BK and opportunistic infections, will be monitored before and after MSC treatment. In our previous small study we found an increased incidence of viral infections [17], however this was not observed in the study by Tan et al. [19].

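### Cotrimoxazole is planned to end close to the MSC infusions, so the before/after change in creatinine-based eGFR may look better than true GFR; iohexol clearance should lead that comparison

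*Protocol article*

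**What the plan says.** All statements are in the protocol article.

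- **(Opportunistic) infections:** "In addition, all patients receive 6 months of cotrimoxazole prophylaxis against PJP". Neither start date nor dose is given.
- **Exclusion criteria, closing paragraph:** patients receive "selected allogeneic MSCs per/kg body weight at weeks 25 and 26 after transplantation". The same paragraph lowers the tacrolimus target from 4–7 to 1.5–3 ng/mL after week 24.
- **Objectives and endpoints:** the secondary endpoints, assessed before and after MSC treatment, include "glomerular filtration rate (GFR) calculated by CKD-EPI formula and measured by iohexol clearance". The two measures stand side by side, unranked.
- **Renal function:** "GFR calculation will be used to determine the renal function", by the CKD-EPI creatinine formula. Then: "In addition we will measure renal function with iohexol clearance at week 24 and week 52 after transplantation".
- **Assessment schedule, Table 1:** routine laboratory tests at every visit; iohexol clearance at W24 and W52 only.
- **Study design:** 10 patients, non-randomized, open label, with no control group.
- **Discussion:** "an important secondary endpoint of our study is renal function before and after MSC treatment".
- **Data collection:** all drugs and dosages are recorded, so individual stop dates should be available.

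**The concern.** In a single-arm before/after comparison, anything that changes for all patients at about the time of treatment is mixed with the treatment effect. Here a background drug that can alter creatinine handling is planned to end at about that time. If it does, the earlier creatinines are taken on the drug and the later ones off it. Serum creatinine may then fall for a reason unrelated to filtration, and the eGFR calculated from it would rise.

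This is a measurement artefact, distinct from a real change in GFR. It runs in one direction, towards better apparent function after MSC, which is the falsely reassuring direction in a safety study. Iohexol clearance does not depend on creatinine and is not exposed to it. The Renal function section, however, gives the calculated value the main role and adds iohexol as a second measure.

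**Working it through.** The article gives no figure for this point, so there is none to reproduce. Two things can be checked: the timing, and what the plan's own formula does with a fall in creatinine.

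**1. Timing, assuming a start at transplantation**

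| Reading of 6 months | Weeks |
|---|---|
| Calendar months: 365.25 / 2 / 7 | 26.1 |
| 30-day months: 6 × 30 / 7 | 25.7 |
| 28-day months: 6 × 28 / 7 | 24.0 |

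The infusions are at weeks 25 and 26. On any of these readings the W24 creatinine is taken on the drug or at its planned end, and the W52 value is off it. W25 may fall on either side. A later start moves the stop further past W24. If the drug ended clearly before the creatinine used as baseline, there would be no bias.

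**2. Size**

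Inputs from the article (Renal function): the CKD-EPI exponent on serum creatinine (SCr) is −1.209 above k and −0.411 (men) or −0.329 (women) below k; k is 0.9 for men and 0.7 for women.

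Input not in the documents: the fall r in serum creatinine when the drug stops. I assume 0 to 15%; zero is possible.

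With sex and race fixed and age practically unchanged, the other terms cancel:

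eGFR after / eGFR before = (1 − r)^(−1.209), if SCr stays above k.

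The proportional eGFR decline that such a step would exactly offset is 1 − (1 − r)^1.209.

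| Assumed r | eGFR rise, SCr above k | eGFR decline offset | Rise from an eGFR of 50 (mL/min/1.73 m²) |
|---|---|---|---|
| 0% | 0% | 0% | 0 |
| 5% | 0.95^(−1.209) = 1.064, +6.4% | 6.0% | +3.2 |
| 10% | 0.90^(−1.209) = 1.136, +13.6% | 12.0% | +6.8 |
| 15% | 0.85^(−1.209) = 1.217, +21.7% | 17.8% | +10.9 |

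Worked example with the full formula: a man aged 50 (race factor 1) with SCr 1.5 mg/dL has an eGFR of 53.5. With r = 10% it becomes 60.8, a rise of 7.3.

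Below k the effect is smaller. At r = 15%, 0.85^(−0.411) = 1.069 for men and 0.85^(−0.329) = 1.055 for women, that is +6.9% and +5.5%.

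**3. Which comparisons are exposed**

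- eGFR, W24 to W52: probably mixes on-drug and off-drug creatinines.
- Iohexol clearance, W24 to W52: not exposed to the artefact.
- eGFR at visits between W24 and W52: the only scheduled GFR information in that window, and it contains the probable stop date.
- eGFR wholly after the stop: no further step, so a progressive decline remains visible.

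**The case against.** The strongest reply has four parts.

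**The mechanism and size come from outside the article.** This stands. The effect on creatinine secretion is general pharmacology that the article does not mention, and neither dose nor start date is given. A reader might infer that eGFR will step up in every patient at the second infusion. The article supports only that it may, at about that time.

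**No early decline is defined as a target.** This also stands. A reader might infer that the artefact hides an early MSC-related decline that the trial sets out to detect. The Discussion reports of an earlier study that "renal function declined when the MSCs were administered 7 days after transplantation". It suggests that infusion timing mattered, and notes no such dysfunction in the group's own cohort treated more than 6 weeks after transplantation. Infusion here is at weeks 25 and 26, and the article sets no early-decline window, threshold or analysis.

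**The remedy is largely in place, and tacrolimus confounds the comparison anyway.** Partly right. Iohexol brackets both infusions and is a named endpoint, but the Renal function section gives the lead to the calculated value. The tacrolimus reduction is a second concurrent change that may alter true GFR, and so iohexol clearance too. It limits attribution to MSC but does not remove the creatinine artefact.

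**Analysis detail belongs in a plan not shown.** True of baseline visit and model. But the article itself fixes the estimator, the iohexol schedule and the relative role of the two measures.

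**Conclusion.** The point holds as a possible bias in a secondary endpoint, not as a demonstrated error. The before/after comparison of CKD-EPI eGFR may be biased towards apparent improvement. Under the assumed 0 to 15% creatinine fall, the bias is 0 to 22% of eGFR with creatinine above k, and less below it. This rests on three assumptions: prophylaxis starts at or after transplantation and runs its planned length; the baseline creatinine is taken before the stop; and stopping lowers creatinine to some degree.

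The documents do not support saying that an early decline will be masked, nor that it could be recovered. With no iohexol value between W24 and W52, a transient early decline cannot be separated from the drug stop. Splitting eGFR into on-drug and off-drug periods would not help, because that split is nearly the same as before and after MSC. The primary endpoint, BPAR and graft loss, is not at issue here.

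**What to change.** In Objectives and endpoints and in Renal function:

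1. Make the change in iohexol clearance from W24 to W52 the lead before/after GFR measure, with CKD-EPI eGFR supportive.
2. Report the within-patient change in the eGFR/iohexol ratio from W24 to W52, as a description of the possible artefact rather than a correction.
3. Plot each patient's eGFR course with the recorded cotrimoxazole stop date marked.
4. State that a rise or plateau in eGFR at about weeks 24 to 30 is not, on its own, evidence of no renal harm.
5. State the limits: no iohexol information between W24 and W52, and a concurrent tacrolimus reduction that may itself change true GFR.

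The cost is wording and a small descriptive analysis of data already planned, with no new visit or procedure. The downside is that the lead contrast rests on two time points in 10 patients. No change to prophylaxis or other clinical management is proposed.

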### Renal function

GFR calculation will be used to determine the renal function [28]. The following abbreviated CKD-EPI formula will be used for GFR estimation: eGFR [mL/min/1.73m2] = 141 × min (SCr/k,1)^α^ × max(SCr/k,1)^−1.209^ × 0.993^age^ × (1.018 if female) × (1.159 if black) (k is 0.7 for females and 0.9 for males, α is −0.329 for females and −0.411 for males). In addition we will measure renal function with iohexol clearance at week 24 and week 52 after transplantation [29].

